### Primary endpoints

The primary study endpoints are a detection rate of early-stage HCC and a false referral rate. The detection rate of early-stage HCC is defined as the proportion of patients having both positive US results and confirmed as having early-stage HCCs on reference standard procedures out of all patients enrolled in the study. The early-stage HCC is defined as a single HCC<5cm or up to three HCCs, each of which is less than 3 cm based on the Barcelona Clinic Liver Cancer staging system (BCLC stage 0 or A) [25]. The false referral rate is defined as the proportion of patients having positive US results but confirmed as not having HCC on reference standard procedures out of all patients enrolled in the study.

The likelihood of HCC = grade 3 will be regarded as test positive both for B-mode US and contrast-enhanced US. If a patient has two or more lesions, the lesion assigned the greatest likelihood of HCC will be regarded as the representative lesion of that patient. As patients who have positive results either on B-mode US or on contrast-enhanced US subsequently undergo reference standard procedures, the true-positives and false referrals are to be determined by comparing the case report forms of each US method with the reference standards. For example, if a patient has a lesion of which the likelihood of HCC is grade 3 on B-mode US but is grade 2 on contrast-enhanced US, and if the patient is finally confirmed as not having HCC on reference standard procedures, it will be counted as a false referral of B-mode US but not of contrast-enhanced US.

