### Sample size

For sample size calculation, we assumed a 5% prevalence of HCC in our target population, a 3.15% detection rate of early-stage HCC on B-mode US (63% of sensitivity)[27],and a4.75% detection rate of early-stage HCC on contrast-enhanced US (95% of sensitivity) [8]. We also assumed a 1.7% discordant rate which included0.05% of the proportion of patients in whom a lesion is detected on B-mode US but not on contrast-enhanced US. With these assumptions, 523patients are needed to obtain 80% statistical power for the McNemar’s test with an α equal to 0.05.

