### Data analysis

While intention-to-treat analysis will be primarily performed for all patients enrolled in the study, per-protocol analysis will also be performed for patients who follow the study protocol without violation. Intra-individual comparison will be made between B-mode US and contrast-enhanced US in terms of the detection rate of early-stage HCC, the false referral rate, and the detection rate of any stage HCC using McNemar’s test in a per-patient manner.

Subgroup analyses will be performed for each endpoint according to a patient’s age, gender, body mass index, cirrhosis etiology, history of anti-viral treatment, Child-Pugh score, Albumin-Bilirubin (ALBI) grade [28], and alpha-fetoprotein (AFP). We will use logistic regression models with a generalized linear mixed model (GLMM) including random intercept for the patients if the study results show considerable variation across the participating institutions. *P* values less than 0.05 are considered statistically significant. All statistical analyses will be performed using commercially available software (SAS Ver. 9.2; SAS Institute, Cary, NC, USA).

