### Study endpoints

The accuracy of a diagnostic test can ideally be evaluated with a definitive diagnosis, usually in terms of sensitivity and specificity. However, studies investigating the efficacy of US in surveillance settings have frequently been limited by verification bias [27]. This is because the definitive diagnostic procedure is used on patients who have positive results, while those who have negative results are not confirmed as true or false negatives, which indicates that neither sensitivity nor specificity is identifiable [29]. A detection rate and a false referral rate are two important reciprocal measures which do not require definitive diagnoses from all study patients and allow a comparison of the relative performance of two screening tests [29, 30]. While we expect improvement of the detection rate of early-stage HCC by adding contrast-enhanced US to conventional B-mode US, the improvement can be truly valuable only if the false referral rate is decreased or at least remains stable.

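### Two unranked primary endpoints are each tested at P<0.05 with no rule for combining them; if either alone can carry a primary claim, the nominal family-wise error is up to 9.75%

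*Protocol article*

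**What the plan says.** - Primary endpoints: "The primary study endpoints are a detection rate of early-stage HCC and a false referral rate". The Abstract and the Design section name the same pair, also without an order.
- Data analysis: the two US methods are compared within patients by McNemar's test "in terms of the detection rate of early-stage HCC, the false referral rate, and the detection rate of any stage HCC". One threshold covers everything: "values less than 0.05 are considered statistically significant". Whether the test is exact, continuity-corrected or uncorrected is not said.
- Sample size: the assumptions concern early-stage detection only, starting from "a 3.15% detection rate of early-stage HCC on B-mode US", and end with "523patients are needed to obtain 80% statistical power for the McNemar’s test with an α equal to 0.05". There is no assumption or power figure for false referrals.
- Discussion, Study endpoints: after stating that a detection gain is expected, the article adds that "the improvement can be truly valuable only if the false referral rate is decreased or at least remains stable".
- Design: enrolment has closed and follow-up for the primary endpoint is still under way.

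**The concern.** Each of two equally ranked primary endpoints can be declared significant at the full 0.05. The methods sections do not say whether one significant result is enough, whether both are needed, or which comes first. The three rules have different error rates and lead to different conclusions. Take a result with detection P=0.20 and false referral P=0.03. It is a significant primary finding if either endpoint suffices and a failed trial under a both-must-hold or detection-first rule. Choosing between these after seeing the data removes the meaning of the 5% level.

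The Discussion's condition is the nearest thing to a rule, but no analysis applies it. A non-significant McNemar test on false referrals would not show that the rate is stable, and no margin or interval is tied to that word.

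**Working it through.** **Inputs from the Sample size section.** Detection 3.15% on B-mode and 4.75% on contrast-enhanced US; total discordance 1.7%, of which 0.05% is B-mode only. Contrast-enhanced only is therefore 1.7% − 0.05% = 1.65%, and the difference is 1.65% − 0.05% = 1.60%. Alpha 0.05, power 80%, N=523.

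**Input not in the article.** Discordance between the methods on false referrals. I assume 1% to 15% of patients and show the range.

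**Step 1: reproduce 523.** Let the number of discordant pairs be Binomial(N, 0.017), with a share 0.0165/0.017 favouring contrast-enhanced US. Summing the rejection probability of the exact two-sided McNemar test at 0.05 gives 79.96% at N=522 and 80.1% at N=523. So 523 is the smallest N that reaches 80%. Normal-approximation formulas at two-sided 0.05 give 519 or 522. The one-sided formula gives 409, so the stated alpha is two-sided.

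**Step 2: nominal error if either endpoint suffices.** A detection success needs a patient with HCC and a false referral needs a patient without it, so the two sets of discordant pairs come from different patients. In a simulation of 400,000 trials, with both null hypotheses true, the correlation between the two rejections was about 0. Treating the tests as independent:

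1 − (1 − 0.05)² = 1 − 0.9025 = 9.75% (upper bound 0.05 + 0.05 = 10%).

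**Step 3: achieved error at N=523.** With s₁ the true size of the detection test (null split 0.85%/0.85%) and s₂ that of the false referral test, the family-wise error is 1 − (1 − s₁)(1 − s₂).

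| Assumed false-referral discordance | Uncorrected (s₁ = 4.39%): s₂ | Family-wise | Exact (s₁ = 2.01%): s₂ | Family-wise |
|---|---|---|---|---|
| 1% | 4.68% | 8.9% | 0.97% | 3.0% |
| 2% | 4.34% | 8.5% | 2.25% | 4.2% |
| 5% | 5.29% | 9.5% | 3.00% | 4.9% |
| 10% | 4.93% | 9.1% | 3.68% | 5.6% |
| 15% | 5.07% | 9.2% | 3.80% | 5.7% |

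The exact test gives less because few discordant pairs are expected for detection (523 × 0.017 ≈ 8.9), which makes it conservative.

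**Step 4: direction.** Each two-sided test has 2.5% nominal error in favour of contrast-enhanced US. For two tests this is 1 − 0.975² = 4.94%.

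**Step 5: other rules.**
- Both must be significant: 0.05 × 0.05 = 0.25% nominal when both nulls hold, and never above 5% when only one holds. Joint power cannot be computed without a false-referral assumption.
- Fixed sequence: at most 5%. Detection keeps the full 0.05, so its power at N=523 stays at 80.1%.
- Equal split, 0.025 each: at most 5%. The exact-test power for detection at N=523 falls to 69.1%, and 80% would need 599 patients.

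**The case against.** The strongest reply is that how two primary endpoints combine is often left to a statistical analysis plan, which is not shown here, and that a journal article condenses. That would answer pure silence. But the article does state a threshold, applies it to both primary endpoints and sizes the trial at the same level for one of them. As written, either can be called significant at the full 0.05.

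Three stronger readings are tempting, and the documents do not support them.

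- A reader might infer that the false-claim rate simply is close to 10%. That needs an either-endpoint rule, which the article never adopts, and the uncorrected test, which it never names. The exact test, which reproduces 523, gives about 3–6%. The 9.75% also counts errors in both directions. The Discussion's condition points towards a joint requirement, under which nothing is inflated.
- A reader might infer that the sample size uses up all the alpha on detection. Powering on one endpoint does not allocate alpha. Under a sequence or a both-must-hold rule each test may use 0.05.
- A reader might infer that the Discussion already implies a testing order. It states a condition, that false referrals fall or stay stable. An order alone would not enforce it: a detection gain with a clear rise in false referrals would still pass the first test.

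What stands of the reply is that the inflation is conditional and may be small. What does not is that the article settles which result decides the trial.

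**Conclusion.** The point holds in a limited form. The article leaves open how two primary endpoints, each tested at 0.05, lead to a conclusion, and it does not bring the Discussion's own condition into the analysis. The size depends on the rule eventually used. For an either-endpoint rule it is up to 9.75% nominal, about 8.5–9.5% with the uncorrected test and about 3–6% with the exact test. For a both-must-hold rule there is no inflation. The achieved figures rest on both nulls being true, the plan's 1.7% detection discordance and my assumed 1–15% for false referrals. The gap should be closed before analysis; it does not invalidate the design or the sample size.

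**What to change.** In Data analysis, before the data are analysed, state that:

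1. The early-stage detection rate, on which the sample size is built, is tested first at two-sided 0.05.
2. The false referral rate is tested at two-sided 0.05 as a confirmatory claim only if detection is significant in favour of contrast-enhanced US. Otherwise it is reported as an estimate with its 95% CI.
3. A detection gain is interpreted together with the false referral difference and its CI, as the Discussion requires. A non-significant difference is not taken as proof of stability. If the sponsor wants a formal claim of stability, it needs a margin and a power statement, neither of which the article gives.
4. The McNemar version is named. The exact test reproduces N=523.

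The cost is a few sentences. N=523 and 80% power for detection are unchanged, whereas an equal alpha split would cut that power to about 69%. The one loss is that a fall in false referrals without a detection gain could not be a confirmatory claim.

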### Secondary endpoints

The secondary endpoints include a detection rate of HCC of any stage adverse event rate of perfluorobutane. The detection rate of HCC of any stage is defined as the proportion of patients having both positive US results and confirmed HCCs of any stage out of the patients enrolled in the study. The adverse event rate is defined as the proportion of patients having an adverse event following injection of perfluorobutane out of the patients enrolled in the study. Short-term and long-term adverse events are to be recorded according to the Common Terminology Criteria for Adverse Events (CTCAE version 4.0) [26] with structured telephone interviews three and 90 days after the surveillance US.

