### Eligibility criteria

Patients aged 20 to 80 years, having liver cirrhosis related to HBV, HCV or primary biliary cirrhosis, and undergoing US for HCC surveillance are eligible for the study. Liver cirrhosis is defined as having one of following criteria [20]: (a) histologically proven liver cirrhosis (METAVIR score 4); (b) endoscopically or radiologically identified esophageal or gastric varices; (c) hepatic surface nodularity seen on a previous cross-sectional imaging study such as US, computed tomography or magnetic resonance imaging; (d)serum platelet count <100,000 /mm^3^; (e) serum albumin <3.5 g/dL; and (f) prothrombin time–international normalized ratio (PT-INR)>1.3. Patients are not eligible for the study if they have history of HCC (either treated or not treated) or a contraindication for the perfluorobutane.

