### US technique

All patients will undergo contrast-enhanced US (Kupffer-phase US ± vascular-phase US) immediately following conventional B-mode US lying in the supine and/or left lateral decubitus position. One of the fellowship-trained abdominal radiologists in each participating institution, and who is aware of the patient’s previous clinical and radiological information, performs B-mode US using an ultrasound system (LOGIQ E9, GE Healthcare, Milwaukee, WI, USA) equipped with a convex transducer operating at a frequency of 1 to 6 megahertz. 16 μg of perfluorobutane is dissolved in 2 mL of sterile water, and the solution is intravenously administrated as a bolus at a dose of 0.015 mL/kg body weight, immediately followed by a 10-mL normal saline flush via the antecubital vein. Ten to 15 minutes after the perfluorobutane administration, the same radiologist performs contrast-enhanced US during the Kupffer-phase with the same ultrasound system. If a new lesion is detected on the preceding B-mode US, vascular-phase US will be performed for the target lesion before the Kupffer- phase and during the arterial (10-40 seconds after administration of perfluorobutane), portal venous (60-90 seconds), and delay (3 minutes)phases. If a new lesion is detected only o n Kupffer-phase US, vascular-phase US will be performed for detecting the target lesion after the Kupffer- phase with re-administration of the same dose of perfluorobutane [9] (Fig. 1). All phases are to be recorded as movie clips. Some representative images, especially in the arterial and Kupffer- phases, are obtained and sent to a picture archiving and communications system (PACS).If there are two or more lesions in a single patient, vascular-phase US will be performed for the largest lesion. In performing US, the radiologists follow the guidelines of the Korean Society of Ultrasound in Medicine [21]. Otherwise, there are no specific restrictions regarding the US technique or time constraint. The scanning parameters are detailed in Table 1.

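### The adverse event rate is divided by all enrolled patients, so any enrolled patient who is never injected would dilute it

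*Protocol article*

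**What the plan says.** The Secondary endpoints section fixes the definition: "The adverse event rate is defined as the proportion of patients having an adverse event following injection of perfluorobutane out of the patients enrolled". It is the only safety endpoint the article defines, and events are collected through "structured telephone interviews three and 90 days after the surveillance US".

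Three other sections bear on who is exposed:

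- US technique plans exposure for everyone: "All patients will undergo contrast-enhanced US (Kupffer-phase US ± vascular-phase US) immediately following conventional B-mode US".
- Eligibility criteria bars patients with "history of HCC (either treated or not treated) or a contraindication for the perfluorobutane".
- Data analysis names two populations: "While intention-to-treat analysis will be primarily performed for all patients enrolled in the study, per-protocol analysis will also be performed". The second is limited to patients without a protocol violation. No population is defined by having received the agent.

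**The concern.** The numerator requires exposure and the denominator does not. A patient who is enrolled but never injected cannot have the event, yet is counted as a patient without it.

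For the detection and false referral rates, an all-enrolled denominator makes sense. Both ultrasound methods are judged on the same patients, and the common denominator keeps the paired comparison intact. That reason does not carry over to an adverse event rate, which describes what happens to people given the agent.

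Neither named population supplies the exposed set. The all-enrolled set can include unexposed patients. The per-protocol set can leave out exposed ones: a patient who was injected but did not have the CT or MRI within the 60 days set under Further imaging work-up could be removed as a violation.

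At stake is a reported safety rate that may be somewhat too low for an agent being assessed as an addition to routine surveillance.

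**Working it through.** **The plan's own figure.** The article gives no expected adverse event rate and no expected share of uninjected patients, so there is no safety figure to reproduce. The one number borrowed from the plan is the sample size: "523patients are needed to obtain 80% statistical power for the McNemar’s test with an α equal to 0.05". It reproduces. The Sample size section gives 1.7% discordance, of which 0.05% is B-mode only, so contrast-only discordance is 1.7% − 0.05% = 1.65%. With these values the exact two-sided McNemar test at 0.05 has power 0.8008 at n = 523, and 523 is the smallest n that reaches 80%. This calculation does not involve the adverse event denominator.

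**Formula.** Let N be the number enrolled, u the share of N not injected, and r the adverse event rate among injected patients.

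- Injected patients: N(1 − u)
- Patients with an event after injection: r × N(1 − u)
- Rate as defined in the article: r × N(1 − u) / N = r(1 − u)
- Relative understatement: [r − r(1 − u)] / r = u

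The understatement does not depend on r or N. It is zero when u = 0 and can never be negative.

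**Numbers.** N = 523 is the planned size; u and r are assumptions.

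| Share not injected (u) | Injected, 523 × (1 − u) | True 1% reported as | True 5% reported as |
|---|---|---|---|
| 0% (the plan) | 523 | 1.00% | 5.00% |
| 1% | about 518 | 0.99% | 4.95% |
| 2% | about 513 | 0.98% | 4.90% |
| 5% | about 497 | 0.95% | 4.75% |
| 10% | about 471 | 0.90% | 4.50% |

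For a true rate of 2.0% and u = 5%, the reported rate would be 2.0% × 0.95 = 1.9%.

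**The case against.** The strongest reply is that the two denominators are meant to coincide. This is a single-arm study in which every patient is to have the contrast examination directly after B-mode ultrasound, and known contraindications are excluded at entry. If the plan is followed, enrolled equals injected and nothing is diluted. This stands, and it rules out the unconditional statement that the safety rate is biased low. A reader might infer that from the definition, but the article reports no uninjected patients and gives no reason to expect many. What remains is that the article itself allows for departures from protocol by planning a per-protocol analysis, and that the definition handles one kind of departure wrongly.

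A second reply is that safety oversight does not depend on this rate. The Stopping rule is triggered by a single life-threatening or fatal serious event, whatever the denominator. This also stands and keeps the severity low.

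Two further criticisms are tempting but not supported:

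- **The upper confidence limit is too low.** By the rule of three, with no events and an assumed 5% uninjected, the limit would be 3/523 = 0.57% rather than 3/497 = 0.60%. The article specifies no confidence interval for this endpoint, so this faults something it does not contain.
- **Patients with one and two injections are pooled.** Under US technique, a new lesion seen only in the Kupffer phase leads to a vascular phase "with re-administration of the same dose of perfluorobutane". A per-patient rate over all exposed patients is nevertheless an ordinary summary of the examination as used. A breakdown by number of injections is a reporting preference that an article may leave to the full protocol or analysis plan.

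**Conclusion.** The point holds in conditional form. The definition counts any enrolled but uninjected patient as event-free and so understates the adverse event rate by exactly the uninjected share. The bias is zero if all are injected. It is 1% to 10% in relative terms if 1% to 10% are not, a range that is assumed because the documents give no figure. The size is probably small, given the same-session design and the exclusion of contraindications. The direction is certain: any error makes the agent look safer. Severity is low, and nothing in the primary endpoints, the McNemar comparisons or the sample size changes.

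**What to change.** In Secondary endpoints, define the denominator of the adverse event rate as patients who received at least one injection of perfluorobutane. Keep all enrolled patients as the denominator for the detection rates and the false referral rate.

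The cost is one sentence, with no new procedure or visit. The case report form completed after contrast-enhanced ultrasound should identify who was examined with the agent. The Design section says that enrolment had closed and follow-up was continuing, so the definition could be corrected before the final analysis. If every enrolled patient was injected, the result is identical, so the change carries no risk.

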### Stopping rule

If one or more life-threatening or fatal serious adverse events (SAEs) are reported in any of study patients, SCAN will be suspended and the study coordinating committee will investigate if the events are attributable to study procedures and determine whether or not SCAN should be terminated early.

### Sample size

For sample size calculation, we assumed a 5% prevalence of HCC in our target population, a 3.15% detection rate of early-stage HCC on B-mode US (63% of sensitivity)[27],and a4.75% detection rate of early-stage HCC on contrast-enhanced US (95% of sensitivity) [8]. We also assumed a 1.7% discordant rate which included0.05% of the proportion of patients in whom a lesion is detected on B-mode US but not on contrast-enhanced US. With these assumptions, 523patients are needed to obtain 80% statistical power for the McNemar’s test with an α equal to 0.05.

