## Background

Currently, clinical practice guidelines recommend semiannual surveillance for patients who are at a high risk of having hepatocellular carcinoma (HCC) [1–4]. While ultrasonography (US) has been used as a standard examination for HCC surveillance [5], the reported sensitivities, varying from 59% to 92% [6], appear to be insufficient to ensure the early detection of HCC. Using US contrast agents, attempts have been made to improve the efficacy of US in diagnosing HCC; however, US contrast agents in surveillance settings have only rarely been validated [6].

Perfluorobutane (Sonazoid; GE Healthcare, Oslo, Norway) is a second-generation US contrast agent, which has unique characteristics allowing Kupffer phase imaging. Kupffer cells, liver-specific macrophages, phagocytize the perfluorobutane [7] and amplify the ultrasound scattering in order to generate the amplified sound wave. Therefore, a hepatic lesion in which the number of Kupffer cells are either markedly decreased or absent shows a defect on US during the Kupffer phase. Perfluorobutane has been studied for various applications such as the diagnosis of focal liver lesions [8–13], grading of the histologic differentiation of HCCs [14, 15], and guidance of surgical or radiological interventions [16–19].

As the Kupffer phase lasts at least 60 minutes with high stability and allows sufficient time to examine the entire liver, we have noted the value of perfluorobutane as a surveillance tool. One earlier, brief report showed that there was improvement in the detection of small HCCs using perfluorobutane [9]. However, it is still unclear whether patients truly benefit from contrast-enhanced US in terms of the detection of early-stage HCC while avoiding unnecessary additional examinations. The purpose of this study is to investigate the added value of contrast-enhanced US to conventional B-mode US as an HCC surveillance tool in patients with liver cirrhosis.

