## Discussion

### Study design

We designed SCAN as an intra-individual comparison study rather than a randomized controlled trial (RCT). Due to the lack of previous researcher grading contrast-enhanced US in surveillance, it was impossible to set the appropriate effect size for an RCT. The lack of baseline data also raised a concern regarding the equipoise that could justify the randomization. Although we could not use the design of an RCT, intra-individual comparison has obvious advantages as it would allow for an excellent comparability between a pair of results and would also increase the statistical power for a given number of study patients. Unlike typical therapeutic or interventional trials, the diagnostic examinations investigated in diagnostic trials can be repeatedly applied to the same patient without affecting the disease status. We expect that the results of SCAN will offer not only the efficacy of contrast-enhanced US but also relevant baseline data for future studies on US surveillance.

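### The early-stage detection rates behind the 523 patients are built on a prevalence of HCC of any stage, so the stated 80% power assumes in effect that every HCC is early-stage

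*Protocol article*

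**What the plan says.** The Sample size section of the protocol article starts from these inputs: "we assumed a 5% prevalence of HCC in our target population, a 3.15% detection rate of early-stage HCC on B-mode US", the latter at a sensitivity of 63%. For the second method it gives 4.75% as the "detection rate of early-stage HCC on contrast-enhanced US (95% of sensitivity"). The total discordant rate is set at 1.7%, of which 0.05% is positive on B-mode only. From these inputs the section derives 523 patients for 80% power with McNemar's test at α = 0.05. It does not say whether the test is exact or asymptotic.

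The Primary endpoints section counts a patient as an early-stage detection only if the confirmed tumour is BCLC stage 0 or A: one HCC under 5 cm, or up to three each under 3 cm. The denominator is all enrolled patients. The Secondary endpoints section lists "a detection rate of HCC of any stage" as a separate measure with the same denominator.

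**The concern.** A detection rate among all enrolled patients is prevalence times sensitivity, and both factors must refer to the same disease. Here the prevalence is that of HCC without regard to stage, while the product is called an early-stage rate. The endpoint definitions treat early-stage HCC as a subset of HCC, so a factor for the early-stage share appears to be missing.

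This is the only power statement in the article, and it concerns a primary endpoint. McNemar's test draws its information from the discordant pairs alone, and very few are expected. A modest cut in the early-stage prevalence therefore removes a noticeable part of the power. A reader weighing a non-significant detection result against a stated 80% would be relying on a figure whose main assumption is not visible.

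**Working it through.** **Inputs (Sample size section).** Prevalence 5%; sensitivities 63% (B-mode) and 95% (contrast-enhanced); discordant rate 1.7%, of which 0.05% is B-mode only; α = 0.05. Two-sided testing is assumed because it reproduces the stated number.

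**Step 1: the rates.**
- 0.05 × 0.63 = 0.0315 and 0.05 × 0.95 = 0.0475. Both match the article exactly, so no early-stage factor was applied.
- Contrast-enhanced only: 1.70% − 0.05% = 1.65%.
- Difference: 1.65% − 0.05% = 1.60% = 4.75% − 3.15%. The cells are internally consistent.

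**Step 2: the plan's own figure.** The number of discordant pairs M follows Bin(n, 0.017). Given M, the number favouring contrast-enhanced US follows Bin(M, 0.0165/0.017). Summing the probability of rejection by the exact two-sided test gives:
- n = 522: 79.96%
- n = 523: 80.08%

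So 523 is the smallest number that reaches 80% with the exact test. The usual normal-approximation formula gives 519. Expected discordant pairs: 523 × 0.017 = 8.9.

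**Step 3: what the rates imply about stage.** Patients detected as early-stage by at least one method make up 4.75% + 0.05% = 4.80% of those enrolled. All of them must have early-stage HCC, and 4.80/5 = 96% of the assumed HCC cases. That is the minimum, before any early-stage tumour missed by both methods. If 95% is the sensitivity for early-stage tumours, early-stage prevalence is 4.75%/0.95 = 5%, a share of 100%. At a share of 0.9, early-stage prevalence would be 4.5%, and a detection rate of 4.75% could not occur.

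**Step 4: power at 523 with an early-stage share f.** The article gives no value for f, so the range is assumed. Both discordant cells are multiplied by f (1.65% × f and 0.05% × f), and the enumeration of Step 2 is repeated for two forms of the test.

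| Share f | Expected discordant pairs (8.891 × f) | Exact McNemar | Uncorrected asymptotic McNemar |
|---|---|---|---|
| 1.0 | 8.9 | 80% | 92% |
| 0.9 | 8.0 | 72% | 88% |
| 0.8 | 7.1 | 63% | 84% |
| 0.7 | 6.2 | 51% | 77% |

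The two columns differ because the counts are so small. Four discordant pairs, all favouring one method, give an uncorrected chi-square of 4²/4 = 4, above the critical 3.84. The exact two-sided p-value for the same data is 2 × 0.5⁴ = 0.125. The exact test needs six pairs, all in one direction (2 × 0.5⁶ = 0.031).

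**The case against.** The strongest reply is that nothing is miscalculated. The 523 reproduces to the patient, and both products are labelled early-stage, so the authors may have meant 5% as the prevalence of early-stage HCC. In that case a brief clarification settles the matter. This is a fair possibility, but the text does not say it, and the paragraph would still need the correction.

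A second reply is that the size of the loss rests on a share the article does not supply and on a test form it does not name. This stands. The table in the working is a sensitivity range, not a demonstrated loss. A reader might infer that 80% power is reached only if every HCC is early-stage. That is true of the exact test, which the 523 matches. With the uncorrected asymptotic test, power is still 81% at a share of 0.75 and drops below 80% only at lower shares.

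A reader might also infer that the remaining inputs were chosen optimistically. The documents do not support that:
- The 59–92% range of US sensitivities in the Background is not labelled early-stage, and its midpoint is not an estimate of B-mode sensitivity for this endpoint.
- The source of the 95% is cited in the Background within a group on diagnosing focal liver lesions. A study from the same group is credited there with better detection of small HCCs, so group membership says nothing about whether the 95% suits surveillance.
- The Discussion's remark that no effect size could be set concerns a randomised trial, not the paired design used here.
- The article gives no basis for a lower contrast-enhanced sensitivity or for a proportion of non-evaluable patients. The primary analysis takes all enrolled patients as its denominator.

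**Conclusion.** The mismatch is real: a prevalence without stage restriction is used to produce early-stage detection rates, although the article's own endpoints separate the two. As written, the rates need at least 96% of HCCs to be early-stage, and 100% if the sensitivities refer to early-stage tumours. The fault lies in the definition of an input and not in the arithmetic.

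The consequence for power depends on two things the article leaves open. Over assumed shares of 0.9 to 0.7, power at 523 runs from 72% down to 51% with the exact test, and from 88% down to 77% with the uncorrected asymptotic test. These figures keep the 5% prevalence, both sensitivities and the ratio of the discordant cells as stated. The endpoint, the paired design and the analysis set are unaffected. This is something the sponsor should fix, and it falls short of a defect that undermines the trial.

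**What to change.** Amend the Sample size paragraph in one of two ways:
- State that the 5% is the prevalence of early-stage (BCLC 0 or A) HCC in the target population, and justify that value; or
- Keep 5% as the prevalence of HCC of any stage, add an explicit early-stage share with its justification, apply it to both detection rates and both discordant cells, and restate the power that 523 patients deliver.

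In either case, name the form of McNemar's test (exact or asymptotic) and use the same form in the power statement and in the analysis.

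The cost is one rewritten paragraph. Enrolment closed in August 2016, and the Design section describes follow-up for the primary endpoint as still ongoing, so no patients are added and no procedure changes. The downside is that, under the second option, the stated power is likely to be less favourable than 80% if the exact test is kept.
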